### Outcome measures

This study includes two co-primary outcome measures, reflecting structural status and functional status.

1. The proportion of people who show ‘disease progression’ in the eye with early AMD during the 12 months of the study based on an increase in drusen volume beyond test-retest repeatability limits or a progression to advanced AMD. Software available for the Cirrus optical coherence tomography (OCT) system allows automated assessment of drusen volume. Irrespective of initial drusen volume, approximately 50% of people with AMD show a significant increase in drusen volume over the 12-month study period, that is, beyond test-retest 95% confidence intervals [42]. Conversion to advanced disease will also be considered to be an indicator of disease progression in this analysis. Data from a trial on a similar group indicates that about 10% of people meeting our inclusion criteria will develop advanced AMD within 12 months [43]. Hence, 60% of participants might be expected to show progression based on increased drusen volume or progression to late AMD. The development of advanced AMD will be determined on the basis of ophthalmologist diagnosis at the monthly follow-up appointments at the nAMD clinic.

2. The rate of retinal adaptation (time taken for photoreceptors to recover their sensitivity after being exposed to a bright adapting light).

Secondary outcome measures include: the change in drusen volume over the 12 month follow-up period; the number of ranibizumab retreatments required during the year in the fellow eye with nAMD (assessed through review of medical records at the end of 12 months); changes in visual function including chromatic thresholds, visual acuity and psychophysical 14 Hz flicker thresholds; self-report outcome measures, including health-related quality of life (EQ-5D) and visual function (VFQ-48) [44]; a sleep quality questionnaire (PSQI) and a semistructured interview (conducted monthly by interview) to determine intervention acceptability.

To obtain detailed information about the time course of any therapeutic action, the primary and the first of the secondary outcome measures (based on drusen volume) will be assessed at baseline and then at monthly intervals (using OCT images obtained at the regular nAMD clinic follow-up appointments).

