The ETDRS visual acuity will be assessed in each eye. Chromatic thresholds will be measured for the eye with early AMD using the Colour Assessment and Diagnosis test [48] (City Occupational Ltd). Contrast thresholds to a 14 Hz flickering stimulus will be measured for the eye with early AMD using the procedure outlined by Dimitrov et al. [49]. The rate of parafoveal cone dark adaptation will be determined for the eye with early AMD using a psychophysical procedure described previously [50]. Thresholds will be determined using a psychophysical method, based on a ‘3 down, 1 up’ staircase paradigm [50]. An array of white light-emitting diodes behind a diffusing filter will be used to light-adapt photoreceptors in the central 43.6° of the test eye (the output of the white light-emitting diodes will be modified by a Lee filter, HT015, to provide a retinal illuminance of 5.20 log phot Td.s^-1^, providing a bleach of 85% cone photopigment and 74% rhodopsin). All light levels fall within the safety guidelines set out in British Standard BS EN 15004-2 (2007) [51]. There will be an initial training phase, of around 5 minutes, then the adapting light will be presented, and finally recovery of visual thresholds will be monitored for 25 minutes after exposure to the adapting light.

Those individuals who are assigned to the treatment group will then be given a light mask, and provided with written and oral instructions on its use. There will also be a reprise of the key information provided in the participant information letter about follow-up appointments. Participants will be given written copies to take home of the PSQI questionnaire that will be used in the monthly interview.

#### **
*Monthly assessment*
**

The investigator will access the OCT images and medical records of all participants after they have attended the ranibizumab clinic for each monthly follow-up appointment. This will allow measurement of drusen volume on a monthly basis, which will allow the final analysis to include an assessment of the time course of any therapeutic action. Additionally, reviewing medical records will facilitate monitoring of the conversion rate to advanced AMD in the control and intervention groups in the eye with early AMD at baseline, and of ranibizumab retreatment rates in the eye with nAMD, for adverse event reporting purposes.

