### Statistical methods

It should be noted that, as a Phase I/IIa proof-of-concept study, this research is designed to assess the acceptability of this therapy for the participants, and to provide preliminary data to support a larger Phase III randomized controlled trial in the future, and so is not powered to detect small effect sizes. To maximize retention, all follow-up visits will be timed to coincide with scheduled appointments at the nAMD clinic. We will aim to recruit 60 people, which, allowing for 15% dropout through the year, should leave a final cohort of 51. This will be sufficient to detect a 50% reduction in people showing progression at a probability level of 0.2, with a power of 80%, and a change in the time constant of cone adaptation of 1 minute to be detected at a probability level of 0.05, with a power of 80%. The additional 40 participants enrolled into the cross-sectional part of the study will allow a total cohort of *n* = 100 to address secondary aim 4.

Analysis will be carried out on an intention-to-treat basis. There will be no interim analysis, but conversions to nAMD in the eye with early AMD at baseline, and ranibizumab retreatments for the fellow eye, will be recorded at each participant visit to the nAMD clinic for safety monitoring purposes.

This trial will primarily be concerned with providing information about the safety of the device in the treatment of AMD, and the magnitude of any treatment effect. On this basis, descriptive statistics will be carried out to summarize the demographic characteristics of the two groups, as well as the proportion of individuals showing disease progression in each group, the magnitude of changes in secondary outcome measures, including drusen volume, measures of visual function, and the self-report tests, and the fellow eye retreatment rates.

The primary outcome measure will be the proportion of patients demonstrating disease progression at 12 months. Comparisons will be performed using stratified Mantel-Haenszel tests and presented as forest plots.

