Formal statistical analysis will also include linear regression analysis to investigate changes in drusen volume controlling for intervention arm, baseline drusen volume and patient characteristics (such as age, vitamin supplement intake and history of smoking). Analysis of covariance (ANCOVA) will be carried out to compare the change in secondary outcome measures (for example, drusen volume, functional tests, self-report measures) and the ranibizumab retreatment rates over 12 months between the two intervention arms, controlling for the characteristics listed previously. Note that all analysis except for the ranibizumab retreatment rate pertains to the eye with early AMD. This will address secondary aim 1. To meet our fourth secondary aim, which is to establish the relationship between baseline functional biomarker outcomes and the severity of AMD, we will carry out a one-way analysis of variance (ANOVA) to compare the mean results at baseline between participants with grades of AMD in each group on the AREDS simplified scale. This analysis will take place when the baseline data collection is complete. To assess the ability of the clinical tests to act as prognostic and predictive biomarkers, receiver operating characteristics curves will be constructed to plot the sensitivity and specificity of the baseline measures in predicting outcomes within the control and intervention arms, respectively. This will address secondary aims 5 and 6. When the trial is completed, linear regression analysis will be used to determine how well the change in the functional measures relate to the change in our primary outcome measure (drusen volume), which is a validated biomarker for disease progression. This will address the seventh secondary aim.

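### Drusen volume is scanned monthly to show the time course of any effect, but no named analysis has a month term, and the 12-month ANCOVA has no outcome for early leavers

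*Protocol article*

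**What the plan says.** **Purpose of the monthly scans.** The Outcome measures section of the protocol article explains the monthly schedule: "To obtain detailed information about the time course of any therapeutic action, the primary and the first of the secondary outcome measures" are to be assessed at baseline and every month after. The monthly assessment text under Data collection methods repeats the purpose and ties it to the analysis: monthly drusen volumes are collected, "which will allow the final analysis to include an assessment of the time course of any therapeutic action".

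**Analyses named.** Statistical methods describes three analyses that bear on drusen volume:
- For the primary outcome: "The primary outcome measure will be the proportion of patients demonstrating disease progression at 12 months". The method is "Comparisons will be performed using stratified Mantel-Haenszel tests and presented as forest plots".
- For drusen volume as a continuous measure: "linear regression analysis to investigate changes in drusen volume controlling for intervention arm, baseline drusen volume and patient characteristics".
- An ANCOVA "to compare the change in secondary outcome measures (for example, drusen volume, functional tests, self-report measures) and the ranibizumab retreatment rates over 12 months". It compares the arms, with the same covariates.

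**Population and follow-up.** The same section states: "Analysis will be carried out on an intention-to-treat basis". It allows for 15% dropout from 60 recruited, leaving 51. The Interventions section withdraws a participant whose study eye converts to neovascular AMD. Outcome measures counts conversion to advanced disease as progression in the primary outcome and expects about 10% to reach it within the year.

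**The concern.** A schedule of a baseline scan and twelve monthly scans is justified by a question about when an effect appears. The models named for the same data have no way to answer it. The article is not silent here: it names the drusen-volume models and their covariates, and those models do not match the purpose it gives for the scans.

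Two things follow if the ANCOVA is fitted as named.
- The timing of any effect, which would inform the length of a Phase III trial, comes from no pre-stated model. Twelve monthly contrasts would then be open to choice after the fact, in a trial where participants and the study investigator know the allocation.
- A participant with several monthly scans but none at month 12 has no outcome value. Some of these are participants whose study eye converted, so their absence is related to how the disease went.

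**Working it through.** **1. Purpose against method**

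| Named analysis | Outcome used | Month or arm-by-month term |
|---|---|---|
| Stratified Mantel-Haenszel | Progressed or not at 12 months | None |
| Linear regression | Changes in drusen volume, visit not named | None |
| ANCOVA | Change over 12 months, one value per participant | None |

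No row gives an arm difference by month.

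**2. The plan's own figure**

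60 × (1 − 0.15) = 51, as stated. With 25.5 per arm, 60% against 30% progressing and a two-sided level of 0.2, power is 0.82, and 24 per arm are needed for 80%. The article does not state sidedness; two-sided without continuity correction fits best. These figures concern the primary outcome, and nothing below changes them.

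**3. Participants with a 12-month change value**

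- If the 15% dropout already includes withdrawn converters: 51 of 60, so 9 without an outcome.
- If the expected 10% come on top: 60 × (1 − 0.15 − 0.10) = 45, or 60 × 0.85 × 0.90 = 45.9. The 10% is advanced AMD of any type, while withdrawal is stated for the neovascular form only.
- With the 12.2% one-year neovascular incidence quoted under Safety monitoring: 60 × (1 − 0.15 − 0.122) = 43.7, or 60 × 0.85 × 0.878 = 44.8.
- At the ends of that figure's interval (1.7% and 30.6%): 50.0 and 32.6 by the subtraction formula.

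So about 51, or about 45 with converters in addition.

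**4. Smallest detectable standardised difference in change**

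Two-sided 0.05, 80% power: (1.960 + 0.842) × √(4/N).

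- N = 60: 0.72 SD
- N = 51: 0.79 SD
- N = 45: 0.84 SD

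**5. What the monthly scans recover at month 12, with month as categories**

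The documents give no within-person correlations. I assumed compound symmetry with 0.5 to 0.9, or first-order autoregressive with 0.8 to 0.95 between adjacent months. Leavers were spread evenly over the year, and the calculation conditions on baseline.

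- 15% missing: effective N is 52.2 to 54.1 instead of 51, a gain of 1.2 to 3.1. The detectable difference moves from 0.79 to between 0.76 and 0.78 SD.
- 25% missing: effective N is 47.0 to 50.1 instead of 45, a gain of 2.0 to 5.1. The detectable difference moves from 0.84 to between 0.79 and 0.82 SD.

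**6. The same question if a straight-line trend holds**

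Let s² be the scan-error variance. For 13 equally spaced scans over one year, the sum of squared time deviations is 182/144 = 1.264. The error part of the variance of the yearly slope is then s²/1.264 = 0.79 s², against 2 s² for the difference of two scans, about 60% less.

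Let r be the scan-error SD divided by the between-person SD of yearly change (not in the documents). The ratio of total variance, complete data, is (1 + 0.791r²)/(1 + 2r²):
- r = 0.25: 0.93
- r = 0.5: 0.80
- r = 1: 0.60

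These savings of 7%, 20% and 40% depend on linearity and on r.

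**7. Size of the covariance model**

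An unstructured covariance over 12 post-baseline months has 12 × 13 / 2 = 78 parameters, which is not workable with at most 60 participants.

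**The case against.** The strongest reply is that the article does commit to assessing the time course and leaves out only the model. An article condenses a fuller plan, and its list of formal analyses is not worded as exhaustive. The time course is also not among the numbered aims, and a covariate-adjusted 12-month change is a valid estimate of effect. Much of this stands:

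- A reader might infer that the time course will never be estimated. The documents do not support that. Data collection methods says the final analysis will be able to include it, and a method may sit in an analysis plan that is not shown. What can be said is that no named analysis estimates it.
- A reader might infer that every drusen-volume analysis uses only the baseline and month-12 scans. Only the ANCOVA is tied to 12 months; the regression names no visit.
- A reader might infer that participants without a 12-month scan are excluded by rule from an intention-to-treat comparison. No such rule is stated. The loss follows from the form of the ANCOVA, and it does not extend to converters in the primary comparison.
- A reader might take the 7% to 40% savings in step 6 as the expected gain. They presuppose the shape of the time course that is to be estimated. The gain in step 5 is much smaller.

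What does not stand is that the matter is wholly left to another document. The article specifies models and covariates for drusen volume, and they do not fit the purpose it states twice. It is fair to add that a mixed model has its own cost: it assumes a covariance or a trend, and it treats outcome-dependent withdrawal as missing at random.

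**Conclusion.** The point holds in a limited form and is worth correcting. Within the article, the stated reason for monthly scanning is not matched by any named analysis. If the ANCOVA is run as named, about 9 of 60 participants have no drusen-volume outcome, or about 15 if withdrawn converters add to the dropout, even though earlier scans exist for those who attended at least one follow-up. The finding is confined to drusen volume as a secondary outcome; the primary outcome and its sample size are untouched.

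The month-12 precision at stake is small, and that estimate rests on the assumed correlations and evenly spread dropout. The case for change therefore rests mainly on delivering the time course from a pre-stated model and on using early leavers' data under a weaker assumption than a completers' analysis needs.

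**What to change.** In Statistical methods, name a repeated-measures mixed model as the main analysis of drusen volume:
- Data: all monthly scans up to conversion or withdrawal, for every randomised participant with at least one post-baseline scan.
- Fixed terms: baseline drusen volume, AREDS stratum, arm, month and arm-by-month.
- Covariance: random intercept and slope, or another parsimonious structure; not unstructured.
- Report: the month-12 arm difference, and the monthly differences as the time course.
- State the missing-at-random assumption and how it will be checked, since withdrawal of converters depends on outcome. State how any reading after conversion is treated.
- Keep the 12-month ANCOVA as a sensitivity analysis.

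The cost is a change of wording and some extra analysis, with no new visits or scans and no change to the withdrawal rule. The price is a covariance or trend assumption, which the retained ANCOVA helps to check, and the missing-at-random assumption, which needs its own sensitivity check.

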## Methods/design

### Trial objectives

The primary aim of this study is to collect preliminary Phase I/IIa proof-of-concept trial data from people with early AMD in one eye and advanced nAMD in the fellow eye, recruited from a hospital nAMD clinic, in order to assess the impact of low-level night-time light therapy, compared with no intervention, on disease progression in the eye with early AMD. A further main aim of this trial is to assess safety of the mask in the cohort of participants with AMD.

The secondary aims of the study are to:

1. Establish the effect of low-level night-time light therapy, compared with no-treatment control, on secondary outcome measures, including: change in drusen volume from baseline in the eye with early AMD; ranibizumab retreatment rates in the fellow eye with nAMD; progression of early AMD on the basis of change in functional outcome measures; change in health-related quality of life (assessed using the EuroQol EQ-5D instrument); change in self-reported visual function assessed using the 48-item Veterans Affairs Low-Vision Visual Functioning Questionnaire (VA LV VFQ-48).

2. Establish the acceptability of low-level night-time light therapy in people with AMD by monthly qualitative interviews.

3. Determine the effect of low-level night-time light therapy on sleep patterns by conducting the Pittsburgh Sleep Quality Index (PSQI) questionnaire every month with both intervention arms by interview with the study investigator.

4. Establish the relationship between baseline functional biomarker outcomes and the severity of AMD (assessed using the simplified Age-Related Eye Disease Scale (AREDS) and initial drusen volume).

5. Evaluate the ability of all clinical tests to act as prognostic biomarkers for AMD progression.

6. Evaluate the ability of all clinical tests to act as predictive biomarkers for low-level night-time light therapy in people with AMD.

7. Compare the sensitivity of all clinical tests to disease progression over 12 months.

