### Recruitment

Sixty participants will be recruited to the trial. Ophthalmologists will identify potential trial participants who are attending for their first appointment at the nAMD clinic at Bristol Eye Hospital, and will provide them with an information sheet and ask for their permission to be contacted by the study investigators. The potential participants will be contacted at least 2 days after their receipt of the information sheet, and invited to meet the study investigator at their next visit to the nAMD clinic (approximately 1 month later) to discuss the trial, provide consent if they choose to participate, and carry out some basic screening tests. Participants will be informed after this screening visit whether they are eligible to take part in the study. Owing to the low number of patients required to participate in the study it is planned for the trial and data collection to take place principally at a single NHS centre, that is, the Bristol Eye Hospital. If needed, additional participants will be recruited from supplementary recruitment centres to ensure that targets are met.

Forty control participants and participants with grade 1 AMD (AREDS simplified scale [45]) for the baseline cross-sectional analysis will be recruited by local optometrists in Bristol and Cardiff, from a database of elderly volunteers, from the Bristol Eye Hospital, from the list of research volunteers at the Cardiff University Eye Clinic and from staff and students of Cardiff University.

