### Randomization

Participants will be stratified according to risk of AMD progression (using the AREDS simplified scale [45]), and randomly allocated to receive either the light mask or no intervention in a 1:1 ratio using computer-generated random permuted blocks (both groups will continue to receive ranibizumab injections as required for the fellow eye). The study investigator will be provided with three piles of envelopes by the chief investigator, in order to randomize the participant to either the intervention or control arm of the study. Each pile relates to a different stratum of randomization, that is, grade 2, 3 or 4 of AMD, according to the AREDS simplified scale. The envelopes in each pile will be numbered, and will contain the randomization allocation for each participant.

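### Secondary aim 4 compares baseline function across AREDS grades without adjusting for age, although low and high grades are recruited through different streams

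*Protocol article*

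**What the plan says.** Under Trial objectives, secondary aim 4 is to "Establish the relationship between baseline functional biomarker outcomes and the severity of AMD". Severity is to be "assessed using the simplified Age-Related Eye Disease Scale (AREDS) and initial drusen volume", that is, by two measures.

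Under Statistical methods, the analysis for this aim is fixed: "we will carry out a one-way analysis of variance (ANOVA) to compare the mean results at baseline between participants with grades of AMD" on the AREDS simplified scale. No covariate is named, and initial drusen volume does not appear in this analysis. In the same paragraph the drusen-volume regression and the ANCOVA for aim 1 are adjusted for patient characteristics, with age as the first example.

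The 100 people in this analysis come from two streams:

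- Under Recruitment, the lower end of the scale is "Forty control participants and participants with grade 1 AMD (AREDS simplified scale [45]) for the baseline cross-sectional analysis". Optometrists in the two cities find some of them, and the university's own employees and students are another listed source. The rest come "from a database of elderly volunteers, from the Bristol Eye Hospital, from the list of research volunteers at the Cardiff University Eye Clinic".
- The upper end is the 60 trial participants, identified at their first nAMD clinic appointment. Under Randomization, "Each pile relates to a different stratum of randomization, that is, grade 2, 3 or 4 of AMD".

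Under Eligibility criteria, the age limits of 55 to 88 years carry no trial-only label, so they apply to both streams. Fellow-eye nAMD is required for the trial only.

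**The concern.** Grade is almost completely aligned with recruitment stream: controls and grade 1 on one side, grades 2 to 4 on the other. Any characteristic that differs between the streams and also affects visual function is therefore confounded with grade. Age is the obvious candidate. The disease is age-related, no age matching is described, and a 33-year eligibility window leaves room for mean ages to differ by several years.

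A one-way ANOVA cannot separate the two. The plan adjusts for age in aim 1, where randomization already protects the comparison, but not in aim 4, which is observational. At stake is the interpretation of the aim for which the 40 extra participants were added: a test that only tracks age could appear to track AMD severity.

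A second, smaller mismatch is that aim 4 defines severity by grade and by initial drusen volume, while the stated analysis uses grade only.

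**Working it through.** **The plan's own figure.** The cohort for aim 4 is 60 + 40 = 100, as stated. No power or significance level is given for this aim, so there is nothing further to reproduce.

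**Inputs from the protocol article.** 40 participants in the lower stream and 60 in the upper; one-way ANOVA with no covariate; age 55 to 88 in both streams.

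**Inputs assumed, because the documents do not give them.** Five groups (controls and grades 1 to 4), taken as 20 each; age SD 8 years within each stream; correlation *r* between age and the functional test of 0.3 to 0.5; two-sided level 0.05; no true effect of grade; mean age gap *d* of 0, 4 or 8 years between the streams, constant within each stream.

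**Formulas.**

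- Spurious difference between streams, in SD units of the test: δ = *r* × *d* / 8.
- Noncentrality of the ANOVA F-test: λ = 100 × 0.4 × 0.6 × δ² = 24 δ². This depends on the 40/60 split, not on how each stream divides into grades.
- False-positive rate: the probability that a noncentral F with 4 and 95 degrees of freedom exceeds the 5% critical value, 2.467.

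| Age gap | *r* | δ | λ | False-positive rate |
|---|---|---|---|---|
| 0 y | any | 0 | 0 | 5.0% |
| 4 y | 0.3 | 0.15 | 0.54 | 7.7% |
| 4 y | 0.4 | 0.20 | 0.96 | 10.0% |
| 4 y | 0.5 | 0.25 | 1.50 | 13.3% |
| 8 y | 0.3 | 0.30 | 2.16 | 17.5% |
| 8 y | 0.4 | 0.40 | 3.84 | 29.4% |
| 8 y | 0.5 | 0.50 | 6.00 | 44.9% |

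A simulation of 4,000 runs per scenario agrees (7.7%, 10.1% and 13.1% for 4 years; 17.5%, 30.3% and 44.9% for 8 years).

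**With age in the model.** The F-test for grade is then exact under these assumptions, so the rate is 5% by construction. Simulated values ran from 4.3% to 6.1%. This return to 5% holds because age is the only confounder in the calculation.

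**Sensitivity to the assumptions.** A 2-year gap gives 5.6% to 6.8% over the same correlations. With age SD 7 instead of 8, a 5-year gap gives 10.9% (*r* = 0.3) to 23.8% (*r* = 0.5), and a 10-year gap gives 33.5% to 78.9%. The range is wide because the two inputs that drive it are unknown.

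**Drusen volume.** No arithmetic is needed. Trial objectives names two severity measures for aim 4, and Statistical methods analyses one. Under Baseline assessment drusen volume is measured, and under Baseline cross-sectional study the 40 extra participants undergo the same tests, so the data will exist for the whole cohort.

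**The case against.** The strongest reply is that no age gap is documented. The lower stream is not simply young volunteers. It includes people found by optometrists, patients of the same eye hospital and a database of elderly volunteers, and the minimum age of 55 excludes nearly all students. If the streams have similar ages, the ANOVA keeps its nominal 5%. This stands, and it is why the point is conditional. A reader might infer that age differences will be mistaken for severity; the documents do not support that, because they give neither ages by source nor an age-function correlation.

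Second, little depends on this result. Prognostic and predictive value are assessed separately by ROC curves (aims 5 and 6), and sensitivity to progression by regression of change (aim 7). A reader might infer that tests would be adopted as biomarkers on the strength of this ANOVA; no section says so. This also stands and limits the weight of the point.

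Third, age adjustment is only a partial remedy. Recruitment source and treated nAMD in the fellow eye stay aligned with grade 2 and above. That is correct. It calls for an added within-trial check, but is no reason to leave age out.

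Fourth, the drusen-volume gap could be condensation in a journal article whose full protocol is not shown. That lowers its weight. Still, the article says its ANOVA meets the aim, and as described it covers only one of the two severity measures.

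Finally, treating the ordered grades as unordered might be called an error. It is not: the omnibus F-test is valid, and a trend test is a choice.

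**Conclusion.** The point holds in conditional form. The article fixes an unadjusted method for an observational comparison in which grade and recruitment stream nearly coincide, so this is a stated choice and not a detail left to another document. If mean age differs between the streams, part of the difference could be read as an effect of severity. Under the assumed values the excess over 5% ranges from none (no gap), through about 3 to 8 percentage points (4 years), to about 12 to 40 percentage points (8 years). These figures show how sensitive the analysis is; they do not estimate a bias known to be present.

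The omission of initial drusen volume is a real but lesser mismatch between aim and analysis. Both matters concern one secondary, cross-sectional aim. Neither touches the co-primary outcomes, safety or the randomized comparison.

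**What to change.** In Statistical methods, make these changes for aim 4:

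1. Replace the one-way ANOVA with a linear model (ANCOVA) of each baseline test on AREDS grade, adjusted for age.
2. Repeat that model within the 60 trial participants (grades 2 to 4) as a sensitivity check. All of them come from the nAMD clinic and have fellow-eye nAMD, so this comparison is free of the stream difference. It gives up the 40 cross-sectional participants and the lower end of the scale, so it supports the main model and does not replace it.
3. Fit the same age-adjusted model with initial drusen volume in place of grade, so that both severity measures in the aim are analysed.
4. State that age adjustment does not remove differences in recruitment source or fellow-eye nAMD between the lower and upper grades.

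A 1-df trend test across grades may be added but is optional.

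The cost is wording only. Age is needed for eligibility, and drusen volume is part of the baseline assessment. The article schedules this analysis for the completion of baseline data collection, so the change should be made before then.

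### The unadjusted one-way ANOVA for secondary aim 4 would confound any age difference between recruitment sources with AMD severity

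*Protocol article*

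**What the plan says.** Trial objectives gives secondary aim 4 as "Establish the relationship between baseline functional biomarker outcomes and the severity of AMD". Statistical methods names the test: "we will carry out a one-way analysis of variance (ANOVA) to compare the mean results at baseline between participants with grades of AMD", with grades taken from the AREDS simplified scale. No covariate is mentioned.

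The sample is pooled. Statistical methods states "The additional 40 participants enrolled into the cross-sectional part of the study will allow a total cohort of" 100 for this aim.

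The two parts of the sample have different origins:

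- **Trial part.** Under Recruitment, "Sixty participants will be recruited to the trial", identified at their first appointment at the hospital nAMD clinic. Under Randomization, "Each pile relates to a different stratum of randomization, that is, grade 2, 3 or 4 of AMD".
- **Cross-sectional part.** Under Recruitment, "Forty control participants and participants with grade 1 AMD (AREDS simplified scale [45]) for the baseline cross-sectional analysis will be recruited by local optometrists". The other sources listed are a database of older volunteers, the Bristol Eye Hospital itself, and recruits "from the list of research volunteers at the Cardiff University Eye Clinic and from staff and students of Cardiff University".

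The age limit of 55 to 88 years in Eligibility criteria is not marked as applying to the trial only, unlike some other criteria, so it reads as covering both parts.

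Elsewhere in Statistical methods, the regression of drusen volume controls for "patient characteristics (such as age, vitamin supplement intake and history of smoking", and the ANCOVAs of secondary outcomes refer back to the same list.

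**The concern.** A one-way ANOVA has one factor. Here that factor, AREDS grade, follows recruitment source: healthy and grade 1 on one side, grades 2 to 4 on the other. Randomisation does not protect this comparison, so if the clinic patients are older on average and the functional measures worsen with age, part or all of a difference between grades could be due to age. The test would then show a severity relation where there is none, or exaggerate a real one.

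The plan adjusts for age where it compares randomised arms, which is where adjustment is least needed to prevent bias. It does not adjust where it compares groups that were never randomised. Aim 4 is also the only analysis for which Statistical methods says the 40 extra participants are needed.

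**Working it through.** **The plan's own figure.** 60 trial participants + 40 cross-sectional participants = 100, as stated. No power, significance level or effect size is given for aim 4, so there is nothing further to reproduce.

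**Inputs from the article.** One-way ANOVA on grade, N = 100, 40 people in the lower grades and 60 in grades 2 to 4, ages 55 to 88.

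**Assumptions, because the article does not give them.** Five groups of 20 (healthy, and grades 1 to 4). Two-sided 5% level. Function changes linearly with age by s = 0.02, 0.04 or 0.06 residual SD per year. The realised mean age gap D between the two sources is varied. Grade itself has no effect.

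**Step 1: the spurious difference.** With no grade effect, the expected difference between the lower and higher grades is s × D. It runs from 0.02 × 2 = 0.04 SD to 0.06 × 10.5 = 0.63 SD.

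**Step 2: what this does to the F test.** The numerator has 4 degrees of freedom and the denominator 100 − 5 = 95. With an age SD of about 6 years within groups, the outcome variance within groups is 1 + 36s². The noncentrality is approximately

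λ = (40 × 60 / 100) × (sD)² / (1 + 36s²) = 24(sD)² / (1 + 36s²).

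For example, s = 0.04 and D = 7 give 24 × 0.28² / 1.0576 = 1.78. The chance that a noncentral F(4, 95) exceeds its 5% critical value is then about 15%.

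**Step 3: all cases.** The simulation drew ages from normal distributions truncated to 55–88. The lower grades were centred at 77 minus a set gap (SD 7) and grades 2 to 4 at 77 (SD 6). Truncation shrinks set gaps of 8 and 12 years to realised gaps of about 7 and 10.5.

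| Realised gap | Approximation, s = 0.02 / 0.04 / 0.06 | Simulated range, unadjusted | Simulated range, age in model |
|---|---|---|---|
| 2 years | 5% / 6% / 6% | about 4–6% | about 4–6% |
| 4 years | 6% / 8% / 12% | about 5–11% | about 4–6% |
| 7 years | 7% / 15% / 29% | about 7–31% | about 4–6% |
| 10.5 years | 10% / 31% / 61% | about 12–60% | about 4–6% |

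The approximation and the simulation agree within a few percentage points, as expected from simulation error and the rounded age SD.

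**Step 4: a second parameterisation.** Here age had SD 7 without truncation, and its correlation with function was 0.2, 0.3 or 0.5. The unadjusted rates were 5.1% / 5.3% / 5.0% with no gap, 6.4% / 6.7% / 10.4% at 3 years, 7.6% / 10.3% / 24.5% at 5 years and 11.0% / 22.9% / 57.3% at 8 years. With age as a covariate the rate stayed between 4.7% and 5.5%. The pattern is the same: no inflation without a gap, little at small gaps, and material inflation once the gap is several years and the age slope is not shallow.

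**The case against.** The strongest reply is that the bias is conditional and its condition is not shown. The article reports no ages by source and no age slope. One low-grade source is explicitly made up of older volunteers, another is the same hospital that supplies the trial patients, and the 55 to 88 limit applies to the 40 as well. If the realised gap is only about 2 years, the planned test stays close to nominal. All of this stands.

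It also rules out two stronger readings. A reader might infer from the mention of staff and students that the comparison group is young. The age limit excludes that. A reader might also infer that a false severity finding is to be expected. The documents support only the weaker statement that any age gap would be confounded with grade. The rates above 30% require a large gap together with a moderate or steep slope.

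A second reply is that a condensed article may leave age-balanced recruitment of the 40 to the full protocol. That is fair, and the absence of matching is not held against the plan here. The test is a different matter: the article names it for a named aim, so it is a stated choice and not a detail left open.

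A third reply is that age adjustment is only a partial remedy. This also stands. The lower and higher grades differ in recruitment route, and every trial participant has nAMD in the fellow eye while the cross-sectional participants are healthy or have early disease only. No age covariate separates grade from those differences.

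**Conclusion.** The concern holds as a conditional one. The stated test for aim 4 cannot distinguish AMD severity from age, and the recruitment scheme makes an age difference between lower and higher grades possible. With no true grade effect, five equal grades and slopes of 0.02 to 0.06 residual SD per year, the false-positive rate ranges from about nominal at a 2-year gap to 12–60% at 10.5 years. The gap, the slope, the grade split and the age distributions are all assumptions, so the size in this trial is unknown.

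The matter is worth correcting because the correction is nearly free and the plan already treats age as a covariate elsewhere. Its reach is limited to one secondary, cross-sectional aim. The randomised comparison, the co-primary outcomes and the safety aim are untouched.

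**What to change.** Replace the one-way ANOVA for aim 4 with a linear model (ANCOVA) of each baseline functional measure on AREDS grade, with age as a prespecified covariate. Report the age distribution by grade, and give age-adjusted grade means with intervals.

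Add a sensitivity analysis restricted to grades 2 to 4, who share one source, keeping age in the model because age may still rise with grade there. It uses the 60 trial participants only, so it is less precise and says nothing about healthy or grade 1 eyes.

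State in the analysis text that age adjustment cannot remove other differences between the sources, such as nAMD in the fellow eye.

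The cost is a line or two of wording and one degree of freedom. Age must already be known for eligibility, so no new data are needed. If age and grade overlap strongly, the intervals for grade will widen.
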